# Efficacy and safety of electric heating moxibustion for perennial allergic rhinitis: protocol for a randomized controlled trial

**DOI:** 10.1186/s13063-019-3550-x

**Published:** 2019-07-19

**Keywords:** Allergic rhinitis, Electric heating moxibustion, Moxibustion, Randomized controlled trial

## Abstract

**Background:**

Allergic rhinitis (AR) is an IgE-mediated disease that adversely affects quality of life. Many studies report that moxibustion is an effective treatment for perennial allergic rhinitis (PAR). However, it is difficult to perform moxibustion on the face because of possible burning of the skin and the noxious effects of smoke. Electric heating moxibustion does not have these limitations. The purpose of this clinical trial is to assess the possibility of treating PAR with electric heating moxibustion and to assess the feasibility of conducting a clinical test on a larger scale.

**Methods:**

This is a randomized, open-label, assessor-blind, parallel-design pilot clinical study. We will recruit 40 eligible participants and randomly allocate them into an electric heating moxibustion group or an acupuncture group at a 1:1 ratio. Patients in both groups will receive eight treatments over 4 weeks, and the final follow-up will be 4 weeks after the last treatment. Eleven acupuncture points will be used for patients in both groups (EX-HN3 and bilateral EX-HN-8, LI20, LI4, GB20, and ST36). The primary outcome measure is change in the Total Nasal Symptom Score, and the secondary outcome measures are changes in the Rhinoconjunctivitis Quality of Life Questionnaire, nasal endoscopy index for pattern identification, pattern identification questionnaire for AR, total IgE, eosinophil count, and adverse effects.

**Discussion:**

This clinical trial will examine the effect of electric heating moxibustion on PAR.

**Trial registration:**

ClinicalTrials.gov, NCT03342105. Registered on 14 November 2017.

**Electronic supplementary material:**

The online version of this article (10.1186/s13063-019-3550-x) contains supplementary material, which is available to authorized users.

## Background

Allergic rhinitis (AR) is a highly prevalent disease that causes physical, psychological, and social problems in daily life [1]. About 10% of the world’s population experience seasonal allergic rhinitis (SAR), and about 10–20% have perennial allergic rhinitis (PAR) [2]. Symptoms of PAR are present in 25% of pre-school children and 75% of school-age children in Korea [3]. The prevalence of PAR seems to have increased in recent years. The prevalence of symptoms related to AR is as high as 31.5% in the USA [4], and a survey of five countries in Europe reported the prevalence of AR was 22.7% [5]. These results thus indicate a high prevalence of AR worldwide.

AR is immunoglobulin E (IgE)-mediated inflammatory response, which can be subdivided into SAR and PAR. The former is caused by seasonal allergens (pollen from *Parietaria*, *Ambrosia*, *Artemisia*, and *Cupressus*) and the latter by perennial allergens (dust mites, animals, occupational factors) [1]. There is some evidence that acupuncture and moxibustion are effective treatments for PAR [6].

Conventional treatment of AR includes avoidance therapy, pharmacotherapy, immunotherapy, and surgery, although avoidance therapy is difficult in clinical practice [7]. Clinicians commonly treat patients with PAR using decongestants, antihistamines, steroids, and antileukotrienes [8]. However, there are limitations to these conventional treatments—no drug can cure PAR, and these treatments have reduced efficacy when taken for a long time and may also cause adverse effects [9]. Thus, there is a need for novel therapies that do not have these limitations [10].

Practitioners of traditional Korean medicine (TKM) have reported the efficacy of acupuncture [11], moxibustion [12], and Korean herbal medicines [13] on AR through various studies. Acupuncture is proven to exhibit anti-inflammatory actions [14] and regulate mediators such as interleukin (IL)-10 [15] and IgE [16]. Moreover, complementary DNA (cDNA) microarray analysis suggested acupuncture treatments as a modulator on the balance between pro- and anti-inflammatory cytokines [9].

Moxibustion is a TKM that aims to prevent and treat diseases by burning of herbal substances at acupuncture points, a process leading to thermal stimulation [17]. From the perspective of TKM, moxibustion treats diseases by encouraging Qi and blood circulation through thermal stimulation and thereby improves the function of internal organs. Various articles have suggested that moxibustion is effective for osteoarthritis-induced pain [18] and chronic fatigue [19] as well as AR [20].

However, conventional moxibustion can cause several adverse effects, especially when used to treat AR. First, facial burning is a potential danger because it is difficult to precisely regulate the temperature of the burning moxibustion [21]. Second, moxibustion releases particulate matter less than 10 μm in diameter (PM10), which is up to five times higher than the World Health Organization (WHO) standard [22], and this may actually exacerbate the AR [23]. Although acupuncture points on the head and face are often used to treat PAR, use of these points for moxibustion may trigger burns and respiratory problems. For these reasons, TKM and other alternative medicines have preferred acupuncture to moxibustion [24]. However, certain medical devices, such as electric heating moxibustion, allow the use of moxibustion without the adverse effects of conventional moxibustion.

This clinical trial will assess the possibility of treating PAR by electric heating moxibustion treatment and assess the feasibility of conducting a clinical test on a larger scale.

## Methods/design

### Objective

This study consists of a parallel clinical test on two groups of patients with PAR, treating one group with electric heating moxibustion and the other with acupuncture. As a pilot study, it seeks to assess the possibility of treating PAR with electric heating moxibustion and the feasibility of conducting a clinical test on a larger scale.

### Hypothesis

The null and alternative hypotheses are the following:H0: μ1 − μ2 = 0 (the null hypothesis, H0). There is no difference in the mean change of the Total Nasal Symptom Score (TNSS) before and after treatment between the moxibustion group and the acupuncture group. This will be tested versus the alternative hypothesis.H1: μ1 − μ2 ≠ 0 (the alternative hypothesis, H1). There is a difference in the mean change of the TNSS before and after treatment between the moxibustion group and the acupuncture group.

The objective is to test whether there is a difference between the mean change of the moxibustion group and the acupuncture group.

### Design and setting

This is a randomized, open-label, assessor-blind, parallel pilot clinical study. This trial will be performed at Dongguk University Ilsan Oriental Hospital in Korea. A total of 40 participants who meet the inclusion and exclusion criteria will be divided into two groups with a 1:1 allocation ratio. The control group will receive acupuncture, and the experimental group will receive electric heating moxibustion. The 8-week study period consists of a 4 week treatment phase and a 4 week follow-up phase.

Figure 1 outlines the trial procedures, and Fig. 2 shows the schedule for enrollment, intervention, and assessments. The Standard Protocol Items: Recommendations for Interventional Trials (SPIRIT) checklist is provided in Additional file 1.

**Fig. 1 Fig1:**
[figure not shown]
Flowchart of this study

**Fig. 2 Fig2:**
[figure not shown]
Schedule of enrollment, intervention, and assessments

### Study subjects

#### Inclusion criteria

The trial inclusion criteria are:Presence of nasal symptoms for 2 successive yearsPresence of at least two nasal symptoms (rhinorrhea, nasal obstruction, nasal itching and sneezing) with severity score of 2 or more (0: no symptoms, 1: mild symptoms, 2: moderate symptoms, and 3: severe symptoms)Testing positive for at least one perennial allergen in a skin prick test (*Dermatophagoides farinae*, *Dermatophagoides pteronyssinus*, dog fur, cat fur, *Alternaria tenuis*, *Aspergillus fumigatus*, or cockroach) [25]Age of 19 to 60 years oldAble to voluntarily agree to participate and to sign informed consentWillingness to participate and sign the informed consent agreement.

#### Exclusion criteria

The exclusion criteria are as follows:Use of drugs that may directly affect AR or skin prick test results; use of nasal/oral corticosteroids within the past month; use of an herbal medication for rhinitis within the past month; use of nasal cromolyn or a tricyclic antidepressant within the past 2 weeks; use of nasal/oral decongestants, nasal/oral antihistamines, or antileukotrienes within the past week; use of drugs the researchers believe are inappropriatePresence of rhinosinusitis, indicated by mucosal thickening or opacification of the paranasal sinuses, as indicated by a paranasal sinus X-rayPresence of a malignant cancer, severe systemic inflammation, or other systemic disease that may affect rhinitisHistory of anaphylaxis in response to allergy testsFemales who are pregnant or lactating (positive reaction to the human chorionic gonadotropin [hCG] test)Having difficulty in maintaining treatment due to paralysis, a severe physical or psychiatric disorder, dementia, drug addiction, or severe visual or audiogenic impairmentBeing afraid of electric heating moxibustion or of the expected adverse effectsConditions which make research participation logistically impossible, such as lack of ability or willingness to make time to participate, to make regular visits to the hospital, or to engage in oral and written communication in Korean.

### Sample size

In the recent systematic reviews on rhinitis with acupuncture and moxibustion, there was no study that used moxibustion alone on PAR [26]. Furthermore, due to the special method of using electric moxibustion, we could not utilize the existing research, and it was necessary to have a flexible approach to statistical design with an exploratory study.

According to the suggestion of Julious [27], the appropriate sample size for a two-arm pilot study should be more than 12. Thus, considering the possibility of dropouts and the other characteristics of this pilot study, we will initially recruit 20 individuals per group.

### Recruitment

Participants will be recruited via outpatient and inpatient clinical recruitment posters. Printed recruitment posters will be distributed in hospital and placed on bulletin boards and websites. The posters will contain a brief introduction to the trial, the details of treatments, and contact information. Participants who wish to participate can directly contact the researcher.

Potential participants will be screened, receive explanations of the trial, and then sign informed consent agreements. Those who meet the selection criteria will receive baseline assessments, and demographic and general medical data will be collected, including medical history, vital signs, skin prick test, physical examination data, radiographic data, and laboratory data to determine eligibility.

### Randomization and blinding

Randomization will be achieved with a computerized random number generator using the stratified block randomization method of SAS (SAS Institute, Inc., Cary, NC, USA). This will be performed by an independent statistician who is not involved in the clinical trial.

The random numbers will be concealed using sequentially numbered, opaque, sealed envelopes. The participant’s envelope is delivered to the site’s code manager. If a participant is enrolled and needs randomization, the envelope will be sent to the TKM doctor who performs the treatment. The doctor will open the envelope in front of the participant. A list of generated codes and SAS programs is kept by statisticians in case of loss.

### Interventions

The treatment will be performed in eight sessions, two times per week for 4 weeks. Follow-up assessment will be conducted at 4 weeks after the end of treatment. Each treatment session will be 15 min in duration. The patients in each group will receive treatment at 11 standard acupuncture points: Yintang (EX-HN3), and bilateral Shangyingxiang (EX-HN-8), Yingxiang (LI20), Hegu (LI4), Fengchi (GB20), and Zusanli (ST36) (Fig. 3). The treatment acupuncture points were selected based on a consensus of TKM doctors, a textbook, literature reviews, and additional studies [28, 29].

**Fig. 3 Fig3:**
[figure not shown]
Acupoints used in this study

#### Electric heating moxibustion

The electric heating moxibustion will be performed at 11 acupuncture points twice per week for 4 weeks using a specially designed device (Cettum, K-Medical Co., Korea) (Fig. 4).

**Fig. 4 Fig4:**
[figure not shown]
**a** Electrical heating moxibustion device, **b** the charging equipment, **c** the power unit, **d** the bottom of the unit

The electric heating moxibustion device has two parts: the heating units and the charging equipment. The practitioner will attach the heating units to the patient’s skin, and the temperature will be set automatically at 10 s after pressing the button on top of the heating unit, as indicated by a change in color of the light-emitting diode (LED) on the button. The temperature will increase to 45 ± 1 °C, remain stable, and then gradually decrease. If a participant complains of unbearable pain or hotness, the attached point will be moved 1 cm or less, based on the judgment of the practitioner.

#### Acupuncture treatment

Acupuncture will be performed at 11 acupuncture points twice per week for 4 weeks using disposable and sterile acupuncture needles (0.25 × 30 mm) (Dongbang Co., Korea).

The guidelines for acupuncture treatment are as follows: the needles will be inserted to a depth of 2–3 mm, perpendicular to the skin surface; there will be no De Qi or reinforcing-reducing manipulation for acupuncture points on the face; and reinforcing-reducing manipulation will be performed by twirling the needle for Hegu (LI4) and Zusanli (ST36).

#### Combined use of medications

Surgical interventions, drugs that may directly affect AR or skin prick test results (nasal/oral corticosteroids, nasal cromolyn, tricyclic antidepressants, nasal/oral decongestants, nasal/oral antihistamines and antileukotrienes), traditional Korean medical treatments (such as acupuncture and herbal medicine to relieve symptoms of AR), newly administered psychotropic drugs, or narcotic analgesics will not be allowed.

Medications that were taken before trial participation will be allowed if the investigators believe they will not affect the interpretation of the outcome. Medications used temporarily for treating new diseases or adverse effects will be allowed pending consultation between the researchers. Detailed information on medications will be recorded in the case report form (CRF).

At the discretion of the physician responsible for the treatment, and based on the medical condition of the subject, if a subject uses a non-allowed medication for treatment during the trial, the subject will be excluded, and this will be recorded in detail on the last page of the CRF.

### Quality assurance

Participants will receive the acupuncture and moxibustion treatment by TKM doctors who satisfy the following requirements:Graduation from a 6-year, full-time course in TKM, taught as a college programCertification by the Korean Ministry of Health and Welfare as a TKM doctorMore than 1 year of postgraduate clinical training in a Korean medicine hospitalCompletion of the first-year residency program in the Department of Acupuncture and Moxibustion at Dongguk University.

Nasal endoscopy and pattern identification will be assessed by TKM doctors who specialize in ophthalmology and otolaryngology.

To reduce bias, the assessor not involved in the randomization and treatment will perform outcome assessment in a separate room from the treatment room.

The practitioners of acupuncture and electric heating moxibustion will receive training on the diagnosis of PAR, the inclusion and exclusion criteria, standard operation procedures, location of the acupuncture points, manipulation techniques of the devices used for electric heating moxibustion and acupuncture, and outcome measures.

### Outcome assessments

#### Primary outcome

The primary outcome measure will be the change of the Total Nasal Symptom Score (TNSS) from baseline (visit 2) to the end of treatment (visit 9). The TNSS evaluates each of four symptoms (rhinorrhea, nasal obstruction, and nasal itching and sneezing) on a 4-point scale (0: no symptoms, 1: mild symptoms, 2: moderate symptoms, 3: severe symptoms], so the total score ranges from 0 to 12 [30].

#### Secondary outcomes

The secondary outcomes are changes in the Rhinoconjunctivitis Quality of Life Questionnaire (RQLQ) score, nasal endoscopy index for pattern identification, pattern identification questionnaire for AR, total IgE, eosinophil count, and the presence of adverse effects. These measures were selected to compare the efficacy, adverse events, and safety of the two treatments, according to Korean Medicine pattern identification.

##### Rhinoconjunctivitis Quality of Life Questionnaire (RQLQ)

The RQLQ is a self-reported questionnaire used to assess the quality of life in patients with AR. The questionnaire has seven domains: activities, sleep, practical problems, nasal symptoms, eye symptoms, emotions, and non-hay fever symptoms [31]. Patients will be asked to recall their experiences during the previous week and to rate each answer using a 7-point scale (0: no impairment, 6: severe impairment). The RQLQ will be administered during visits 2, 6, 9, and 10.

##### Nasal endoscopy and pattern identification

These measures consist of an index and a questionnaire:*Nasal endoscopy index for pattern identification*. The investigator (a TKM doctor) will evaluate the nasal endoscopy index during visits 2 and 9. The investigator will determine the score based on observations of the nasal membrane color, the presence of rhinorrhea, and the presence of inferior turbinate swelling (using nasal endoscopy) [32].*Pattern identification questionnaire for AR*. The investigator (a TKM doctor) will select a pattern for each patient (Lung Heat, Lung Cold, and Spleen Qi Deficiency) by face-to-face diagnosis and based on body and nasal conditions [33].

##### Total IgE, eosinophil count

Total serum IgE and eosinophil count levels will be measured during visits 2 and 9.

##### Adverse effects

Any unexpected symptoms will be checked at every visit, and their time of occurrence and duration will be recorded.

### Adverse events

Previous studies reported that common adverse events caused by moxibustion were blister, redness, itching, burns, keloids, discoloration, and allergic reaction to the tape [34]. Common adverse events caused by acupuncture were bruising, peripheral neuritis, cellulitis, allergic reaction, pain lasting more than 2 weeks, and dermal hypersensitivity [34].

At every visit, the participants will report adverse events, and the investigator will record the details, including the specific symptom, onset, duration, severity, time of resolution, and possible association with treatment. The practitioner will decide whether to pause treatment, depending on the severity, to prevent exacerbation. The practitioner will also measure vital signs at every visit.

### Dropout

Participants who meet any of the following criteria will be excluded from the trial, and the specific reasons will be fully recorded: withdrawal of consent; new surgical intervention, injection, or oral drug for treatment of rhinitis during clinical trial period; receiving fewer than six treatment sessions or not participating in the follow-up; experiencing severe adverse events making further inclusion in the trial unsustainable; and if the researcher determines that further participation is inappropriate.

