### Withdrawal and discontinuation

Participants can withdraw voluntarily at any time during the trial. Participants who are unable to complete the study, regardless of time or reason, are considered dropouts. The last recorded data for these participants will be included in the data analysis.

Withdrawal due to adverse events is distinguished from withdrawal due to inadequate response. All adverse effects are analyzed at the study endpoint regardless of whether they are considered relevant to the study treatment or not. If a participant withdraws due to a serious adverse event, it will be reported according to the reporting requirements. Where appropriate, data collected by these participants will be used in intention-to-treat analyses.

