### Statistical analysis

An independent statistician blinded to group allocation will perform statistical analysis on the full analysis set (FAS) and will also perform a per-protocol (PP) analysis. Missing data imputation (last observation carried forward [LOCF]) will be used to evaluate the robustness of the primary endpoint. The null hypothesis is that the two groups have no changes in any of the outcome variables.

The independent-samples *t* test or the Mann-Whitney test will be used to compare the primary outcomes between the two groups. For the primary outcome measure, a repeated measures analysis of variance (ANOVA) will also be used to test the effect of time and the treatment cross-effect.

For secondary outcome measures, the independent-samples *t* test or the Mann-Whitney test will be used to analyze continuous variables, and the chi-squared test to analyze categorical variables. For safety outcomes, the incidence of adverse events will be determined, and the two groups will be compared. A *P* value below 0.05 will be considered statistically significant.

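### The rules for participants who meet a dropout criterion conflict, and do not say whether their visit 9 outcome is collected and analysed

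*Protocol article*

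**What the plan says.** Four sections of the protocol article govern the same people.

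- **Dropout:** "Participants who meet any of the following criteria will be excluded from the trial, and the specific reasons will be fully recorded". The criteria are withdrawn consent; a new operation, injection or oral drug for rhinitis; "receiving fewer than six treatment sessions or not participating in the follow-up"; severe adverse events; and a discretionary ground, "if the researcher determines that further participation is inappropriate".
- **Combined use of medications:** a participant who takes a non-allowed medication during the trial is excluded, with a note in the case report form.
- **Withdrawal and discontinuation:** anyone who does not complete, at whatever time and for whatever cause, counts as a dropout. "The last recorded data for these participants will be included in the data analysis". The section closes with: "Where appropriate, data collected by these participants will be used in intention-to-treat analyses".
- **Statistical analysis:** the statistician "will perform statistical analysis on the full analysis set (FAS) and will also perform a per-protocol (PP) analysis". LOCF is named as a way to check the robustness of the primary endpoint.

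On timing, the primary outcome is the change in the Total Nasal Symptom Score (TNSS) from visit 2 to visit 9, the end of treatment. The only thing the article calls follow-up comes 4 weeks later. The visit list for the quality-of-life questionnaire ends at visit 10, so visit 10 is taken here to be that follow-up.

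**The concern.** Apart from withdrawn consent, every criterion depends on what happens to the participant under treatment. Starting a rhinitis drug plausibly signals poor response. Adverse events may differ by arm, since the Adverse events section lists different profiles for the two treatments. Researcher judgement is exercised in an open-label trial. If such participants leave the primary comparison, or stop being assessed before visit 9, the remaining groups may no longer be the groups that were randomised.

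The wording also leaves room to decide after the event whose data count. One sentence includes dropouts' data without condition, and a later sentence in the same section makes inclusion conditional.

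**Working it through.** **Step 1. Set the rules side by side for two kinds of participant.**

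*A participant who attends through visit 9 and misses only visit 10.* The primary outcome is complete. The Dropout section nevertheless excludes this person. No participation is left to stop, so the exclusion has little meaning unless it means discarding data. Withdrawal and discontinuation says the recorded data are analysed. The two rules point in opposite directions. If the second is followed, the primary comparison loses nothing.

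*A participant excluded before visit 9 for rhinitis treatment, few sessions, an adverse event or researcher judgement.* If exclusion ends assessment, no visit 9 TNSS exists. Withdrawal and discontinuation would use the last recorded value. Statistical analysis reserves carrying forward for a robustness check, so it is unclear whether this person enters the main comparison. At best an earlier value stands in for one that could have been collected.

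**Step 2. Size of the bias if exclusions do reach the primary comparison.** The article gives no dropout rate, no SD and no link between exclusion and outcome, so every rate and correlation below is an assumption. Let the true difference be 0, let fractions a and b be excluded in the two arms, and let ρ be the correlation between the tendency to be excluded and a poor outcome. Then

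bias (SD) = ρ × [φ(z_a)/(1−a) − φ(z_b)/(1−b)],

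where φ is the normal density and z_a and z_b are the normal cut-offs for those fractions. The bracketed terms are 0.109 at 5%, 0.195 at 10%, 0.274 at 15%, 0.350 at 20%, 0.424 at 25% and 0.497 at 30%.

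For example, 20% against 5% with ρ = 0.5 gives 0.5 × (0.350 − 0.109) = 0.12 SD. A simulation of the two-sided t test with 20 randomised per arm (40,000 runs) agrees:

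| Excluded, arm 1 / arm 2 | ρ | Bias (SD) | Type I error |
|---|---|---|---|
| 20% / 20% | 0 | about 0 | 0.051 |
| 20% / 5% | 0 | about 0 | 0.049 |
| 20% / 20% | 0.5 | about 0 | 0.051 |
| 20% / 5% | 0.5 | 0.12 | 0.064 |
| 30% / 10% | 0.5 | 0.15 | 0.071 |
| 20% / 5% | 0.8 | 0.19 | 0.089 |
| 30% / 5% | 0.8 | 0.31 | 0.152 |

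The bias favours the arm that loses more poor responders. With a perfect link (ρ = 1), 15% against 5% gives 0.17 SD and 25% against 5% gives 0.32 SD.

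**Step 3. Loss of precision.** The 95% CI half-width is t(0.975, 2n−2) × √(2/n). At the planned 20 per arm it is 0.64 SD. If 16 per arm remained (an assumed loss of 4), it would be 0.72 SD. The difference detectable with 80% power would rise from 0.91 SD to 1.02 SD.

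**The case against.** A reader might infer that the dropout rule removes these participants from the FAS, collapses it into the per-protocol set and so biases the primary comparison. The documents do not support that. The Dropout section speaks of exclusion from the trial and names no analysis set. Two of its criteria are worded in terms of further inclusion or participation, which is the language of stopping. The next section keeps dropouts' last recorded data, and a separate per-protocol analysis is planned. Read together, the sections can mean that participation stops, data stay in the FAS and only the per-protocol set is restricted. On that reading a missed visit 10 adds no bias to the visit 9 comparison.

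Three further points are fair:

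- The conditional sentence on intention-to-treat use follows one about serious adverse events, so it may concern only those withdrawals.
- A formal definition of the FAS may sit in the full protocol or analysis plan, and its absence from the article is no finding.
- This is a 40-person feasibility pilot that recruits 20 per group against a guide of more than 12, with dropouts in mind.

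These points limit the claim but do not remove it. The charitable reading has to be assembled by the reader, and it does not explain exclusion for missing a visit after the primary endpoint. It also leaves visit 9 outcomes uncollected for people stopped earlier. Pilot or not, the trial tests a null hypothesis at P < 0.05.

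**Conclusion.** The point holds as an unreconciled conflict between the four sections, with a conditional risk of bias. The missed follow-up is the plainest inconsistency but carries little risk if recorded data are kept. The rhinitis-treatment, few-sessions, adverse-event and researcher-judgement criteria carry more, because they can cost the primary outcome itself, possibly unevenly by arm.

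The bias is about 0 if exclusions are balanced between arms or unrelated to outcome. It is roughly 0.1 to 0.3 SD, with type I error between about 0.06 and 0.15, only where exclusions are both uneven and outcome-related, as in the assumed scenarios. At an assumed TNSS SD of 2.5, the simulated 0.12 to 0.31 SD is about 0.3 to 0.8 points (0.12 × 2.5 and 0.31 × 2.5). None of the rates, correlations or the SD comes from the article.

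**What to change.** Reconcile Combined use of medications, Dropout, Withdrawal and discontinuation, and Statistical analysis, as follows:

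1. State that the dropout and non-allowed-medication criteria define per-protocol status only.
2. Keep all randomised participants in the FAS in the arm to which they were randomised, using the visit 9 TNSS wherever it is available.
3. Continue to collect visit 9 and visit 10 outcomes after a criterion is met, unless consent is withdrawn.
4. Drop non-participation in the follow-up as a ground for exclusion from the visit 9 analysis.
5. Delete the opening two-word qualifier from the sentence on intention-to-treat use, so that one rule applies to all dropouts.

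The cost is a change of wording and a few extra outcome assessments. Clinical decisions to stop treatment are unaffected. The change should be made before allocation is linked to outcome data.
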